### Sample size

This study adopts a three-arm design to evaluate the eHealth intervention’s superiority to usual care and non-inferiority to face-to-face intervention using a hierarchical testing procedure.^63^ The trial will be termed successful if superiority of the eHealth intervention to usual care as well as non-inferiority of the eHealth intervention to the face-to-face intervention has been shown. A hierarchical testing procedure will be applied, first testing superiority, followed by testing non-inferiority if and only if superiority was shown. Consequently, no correction for multiple testing needs to be applied. Note that if superiority was shown, but showing non-inferiority failed, it is still allowed to conclude that eHealth intervention is effective, but not that it can replace the face-to-face intervention.

The primary outcome used to test superiority as well as non-inferiority is the PDI measured at 6 months. Both tests will be based on the comparison of the mean value after correction for the baseline PDI (Analysis of Covariance (ANCOVA) approach). The assumed SD of the PDI and the correlation between baseline and 6 months equal 15 and 0.65, respectively, and were obtained from pilot data on 28 subjects.^45^ No difference in PDI was expected between face-to-face and eHealth self-management and the region of non-inferiority was defined as a difference of five PDI points. The sample size was calculated to have at least 80% power to show non-inferiority based on a one-sided test with alpha equal to 0.025 (hence, equivalent to a two-sided test with alpha=0.05). A simulation study with 2000 simulations was used, and the power was defined as the percentage of sampled datasets where non-inferiority has been shown using the ANCOVA approach. With 79 subjects in the eHealth and the face-to-face group, there is at least 80% power to show non-inferiority.

To show superiority of eHealth intervention vs usual care based on a two-sided (ANCOVA) test with alpha equal to 0.05, 83 subjects per group are required to detect with at least 80% power a difference of 5 points. Note that having at least 80% power for each of the two comparisons separately does not guarantee 80% power simultaneously.

Strictly speaking, fewer patients are required in the face-to-face group compared with the two other groups. However, given the small difference (79 vs 83), it was decided to recruit an equal number of patients in each of the three groups.

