Based on the number of subjects required for the primary outcome, more than 80% power is also guaranteed for the key-secondary outcome Survey of Pain Attitudes (SOPA). Indeed, to detect a difference in SOPA of 4 points, assuming an SD of 7.5 and a correlation between baseline and 6 months of 0.30, 52 subjects per group are required. Further, 50 subjects per group are required to show with at least 80% power non-inferiority of eHealth intervention, setting the margin of non-inferiority equal to 4 points. Assumptions for the key secondary outcome measure are based on the pilot study of Moseley *et al* on PSE in a non-cancer population.^64^

To anticipate a dropout percentage of 7%, the sample size in each group will be increased with factor 100/93=1.075, yielding 90 subjects per group, hence 270 subjects in total.

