### Data analysis

A constrained longitudinal data analysis model (cLDA) will be used to compare the PDI between the three groups.^65^ In the cLDA, both the baseline and post-baseline values (12 weeks, 6 months and 12 months) are modelled as dependent variables, as opposed to a (longitudinal) ANCOVA model in which the baseline value is included as a covariate. Although the baseline measure is included in the response vector in cLDA, the true baseline means are constrained to be the same for different treatment groups due to randomisation, and this analysis provides an adjustment for the observed baseline difference in estimating the treatment effects. As opposed to the ANCOVA model, the cLDA approach can handle the presence of missing data and produces unbiased estimates if the missing data mechanism is missing at random. Additionally, 95% CIs for the group-specific mean post-baseline values will be constructed as well as the confidence intervals for the differences between the groups. The stratification variable will be added as a fixed factor in the model.

The primary analysis refers to the comparison after 6 months. A hierarchical testing procedure will be applied for the two primary comparisons. First, the difference between the eHealth intervention and usual care will be tested based on a two-sided test with alpha set at 0.05. If significant, non-inferiority of the eHealth intervention vs the face-to-face intervention will be tested based on a one-sided non-inferiority test with alpha set at 0.025 and defining the margin of non-inferiority as a difference of 5 PDI points. For the superiority comparison, the analysis will be based on the intention-to-treat principle, that is, all randomised patients will be analysed in the allocated group. However, for the non-inferiority comparison, the analysis will be based on the as-treated analysis set.

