For the continuous secondary outcomes, the same cLDA model as for the primary outcome will be used. For the key-secondary outcome SOPA, a non-inferiority test (eHealth vs face-to-face intervention) will be performed defining the margin of non-inferiority as a difference of 4 points (one-sided test with alpha equal to 0.025). Note that for the other secondary outcomes, no inferiority tests will be performed, but all differences between groups will be evaluated using two-sided 95% CIs. The alpha-level for the secondary outcomes is set at 0.05, without a priori planned corrections for multiple testing. Thus, only for the key-secondary outcome SOPA a strong claim is possible without correction for multiple testing. Data analysis will be performed by The Leuven Biostatistics and Statistical Bioinformatics Centre of KU Leuven, who is blinded to group allocation.

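### The protocol says SOPA supports a strong claim without multiplicity correction, but SOPA lies outside the fixed testing sequence, so the statement does not follow

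*Protocol article*

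**What the plan says.** The protocol article defines a sequence under Sample size: "first testing superiority, followed by testing non-inferiority if and only if superiority was shown". From that it derives: "Consequently, no correction for multiple testing needs to be applied". The Data analysis section confirms the scope: "A hierarchical testing procedure will be applied for the two primary comparisons". In it, the eHealth versus usual care difference in PDI at 6 months "will be tested based on a two-sided test with alpha set at 0.05". If that is significant, eHealth versus face-to-face follows, by a "one-sided non-inferiority test with alpha set at 0.025" and a 5-point margin.

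SOPA appears in two places.

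- **Sample size** gives 52 per group "to detect a difference in SOPA of 4 points" and, in addition, 50 per group for non-inferiority with a 4-point margin. The difference test has no named comparator and no alpha of its own.
- **Data analysis** specifies a SOPA non-inferiority test of eHealth against face-to-face ("one-sided test with alpha equal to 0.025"). It sets alpha at 0.05 for the secondary outcomes with no planned correction, and then concludes: "Thus, only for the key-secondary outcome SOPA a strong claim is possible without correction for multiple testing".

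Nowhere is a SOPA test made conditional on a PDI result. No order or alpha split between the two SOPA analyses is given.

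**The concern.** For PDI the reasoning is sound. The second test is reached only if the first succeeds, so both can run at full level. For SOPA the same freedom from correction is asserted without that mechanism. Calling an outcome key secondary, or powering it separately, does not control the error rate once the full alpha has been spent on PDI.

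As written, a strong SOPA claim would be open to the investigators even if PDI superiority failed. A reader would have no means of knowing that this claim carries extra error on top of the primary sequence.

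**Working it through.** **1. The plan's own sample sizes, each test at full alpha.** Use n per group = 2(1.960 + 0.842)² × s² / d², where s = SD × √(1 − r²) is the ANCOVA residual SD. All inputs come from Sample size.

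- SOPA: s = 7.5 × √(1 − 0.30²) = 7.155 and d = 4, giving 50.2, so 51. The stated 52 for the difference test has 80.6% power by the noncentral t, so it reproduces. The stated 50 for non-inferiority has 79.8% (normal) or 79.0% (t), which is within a patient or two.
- PDI superiority: s = 15 × √(1 − 0.65²) = 11.399 and d = 5, giving 81.6, so 82. The stated 83 has 80.2% power by t, so it reproduces. With dropout, 83 × 100/93 = 89.2, so 90.

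The SOPA sizes thus correspond to tests at uncorrected levels.

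**2. PDI sequence plus the one explicit SOPA test.** Take all nulls as true, with each non-inferiority null at its margin. The PDI sequence makes a false claim only if its first step rejects, which has probability 0.05 two-sided or 0.025 in favour of eHealth. The SOPA non-inferiority test rejects falsely with probability 0.025.

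With independent outcomes:

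- at least one false claim: 1 − 0.95 × 0.975 = 7.4%, against 5%
- in favour of eHealth only: 1 − 0.975 × 0.975 = 4.9%, against 2.5%

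The two tests share the eHealth arm. With equal allocation, the correlation between the two comparisons on a single outcome is 0.5. A PDI–SOPA correlation of r therefore makes the two test statistics correlate 0.5r. The protocol gives no r, so a range is shown (bivariate normal):

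| Assumed r | Any false claim | In favour of eHealth |
|---|---|---|
| 0 | 7.4% | 4.9% |
| 0.3 | 7.3% | 4.9% |
| 0.5 | 7.3% | 4.8% |
| 0.7 | 7.2% | 4.7% |

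**3. If the SOPA difference test is also run at 0.05.** This assumes usual care as its comparator. Simulation with 2,000,000 draws, on the same basis:

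- SOPA pair alone: about 7.0% (upper bound 0.05 + 0.025 = 7.5%). In favour of eHealth, about 4.5% (bound 5%).
- PDI sequence plus both SOPA tests: 11.7% at r = 0, falling to 10.3% at r = 0.7 (bound 12.5%). In favour of eHealth, 6.9% falling to 6.1% (bound 7.5%).

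**4. What placing SOPA after PDI would do.** In a single fixed sequence, a false claim needs a false rejection at the first true null, so the total stays at 5% two-sided, or 2.5% in favour of eHealth. The price is power. With 83 per group the PDI noncentrality is 5 / (11.399 × √(2/83)) = 2.826, and each PDI test has Φ(2.826 − 1.960) = 80.7% power. With correlation 0.5 from the shared arm, both succeed together 69.6% of the time (normal approximation). A SOPA claim placed after both is therefore out of reach in about 30% of trials even if every planned PDI assumption holds. On its own, a SOPA test at 83 per group has about 94.7% power.

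**The case against.** Several counter-arguments have weight.

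- **SOPA is openly secondary.** Trial success is defined by the two PDI tests alone, and the protocol admits that secondary outcomes are uncorrected. The sentence can be read as contrasting one prespecified, separately powered outcome with many others, and a strong claim is never defined. This stands in part. A reader might infer that the trial promises SOPA the same protection as the primary, but the protocol does not say that. It does say that a strong claim is available without correction, and presents this as a consequence of what precedes it. It is not one.
- **Only one SOPA test is explicit in the analysis section.** This stands. The difference test is inferred from the sample size text and the general 0.05 level. A reader might take 11% to 12% as the plan's error rate. That figure needs the inferred test, every null true, little PDI–SOPA correlation, and results against eHealth counted as false claims. The point does not need it, because one SOPA test outside the sequence is enough.
- **A statistical analysis plan may order the secondary tests.** It may, and a missing order would not be a fault in an article. The objection here is to a positive statement. If a later plan made SOPA conditional on PDI, the published sentence would still need rewording.
- **SOPA at 6 weeks has its own objective, the education part alone, and tying it to 6-month disability is a design choice.** This stands, and it is why the fix offers a choice. Splitting alpha between the two SOPA tests is affordable (61 per group each, about 91% power at 83), but it controls error within SOPA only and would not justify the sentence alongside PDI.

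**Conclusion.** The sentence is wrong as written: the stated procedure does not give SOPA the error control needed for a strong claim without correction. With the explicit SOPA non-inferiority test alone, the chance of at least one false claim is about 7.2% to 7.4% against 5%, or 4.7% to 4.9% against 2.5% in favour of eHealth. If the difference test is added, it is about 10% to 12%, or 6% to 7% in favour of eHealth, and about 7% for the SOPA pair alone.

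All figures assume that every null is true, with SOPA non-inferiority exactly at its margin, and a PDI–SOPA correlation of 0 to 0.7. They show that familywise control is absent. They do not predict the error in this trial. Each test keeps its own nominal level, the PDI sequence is valid, and nothing here weakens the primary conclusion.

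**What to change.** Choose one of two changes.

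1. Delete the concluding sentence on SOPA and report SOPA as a supportive result, as an estimate with its 95% confidence interval. The non-inferiority margin can stay as a reference for interpretation. The cost is one sentence and the confirmatory status of SOPA.
2. Keep the strong claim, but list the SOPA test or tests, in a stated order and with comparator and alpha named, as the next steps of the fixed sequence after the two PDI tests. Allow the claim only if every earlier step succeeded, and otherwise report the estimate and interval. State also that the power of more than 80% given for SOPA applies before this condition, since both PDI tests succeed together only about 70% of the time on the plan's assumptions with 83 per group.

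The second option needs no extra patients and about one paragraph of text. Its downside is that a confirmatory SOPA claim is lost whenever an earlier step fails. Recruitment is expected to run until January 2028, so either change can be made well before the data are analysed.

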### Data security and management

Participant data will be stored on a secure database (REDCap) in accordance with the General Data Protection Regulations (2018). Data are de-identified and a unique trial identification number used on all participant communication. Clinical and patient forms will be checked for completeness and congruity before data entry onto the database. Data will undergo additional checks to ensure consistency between data submitted and original paper forms. Trial documentation and data will be archived for at least 10 years after completion of the trial.

### Trial monitoring

The trial steering committee will oversee all aspects of design, delivery, quality assurance and data analyses. The trial steering committee does not have direct access to the data, but may have access to reports on data quality, for example. The data monitoring committee will check completeness, validity and data quality and report to the trial steering committee about this.

## Ethics and dissemination

### Ethical considerations

The PECAN trial applies the principles established in the Declaration of Helsinki.^66^ Participants provide written informed consent before data collection. Only de-identified coded and interpreted data will be shared between the members of the research team. Ethical approval was granted by the Ethical Committee of the University Hospitals Leuven and Antwerp: BUN B3002023000132

### Dissemination of results

The research team is committed to full disclosure of the results of the trial. Findings will be reported following CONSORT guidelines, and we aim to publish in high-impact journals. The funder will take no role in the analysis or interpretation of trial results.

## Discussion

This protocol describes a pragmatic, three-arm randomised controlled trial evaluating the effectiveness of an innovative eHealth self-management support programme for persistent pain after breast cancer treatment. By comparing the eHealth intervention to both usual care and a face-to-face programme, the study aims to assess its superiority and non-inferiority, respectively. The intervention is grounded in a biopsychosocial model and leverages PSE and behaviour change principles to promote an active lifestyle. Delivered via a chatbot, the programme is designed to be accessible, scalable and cost-effective. Its digital format offers the potential to overcome common barriers to pain rehabilitation, such as limited availability of specialised care and time constraints. The trial is conducted in both hospital and primary care settings to enhance external validity. Pain-related disability at 6 months is the primary outcome, supported by a broad set of secondary outcomes assessing physical, psychological and health-economic effects. Patient input informed the design, ensuring relevance and feasibility. Results from this trial will contribute valuable evidence on the role of eHealth self-management in cancer-related pain rehabilitation and inform future implementation strategies.
